## Abstract

**Background:**

Teleaudiology can potentially improve access to hearing healthcare services. Remote hearing aid fittings offer a new mode of service delivery that removes barriers of geography and access to an audiologist. Real-ear measurements (REMs) are the gold standard for hearing aid output verification but require in-clinic appointments. This study will investigate whether remote hearing aid fittings can provide clinically equivalent outcomes when compared to current, in-clinic, best practice guidelines.

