**Conclusions:**

This study will inform the development of best practice guidelines for remote hearing aid fittings. If no clinically significant differences are found between in-clinic and remote fit hearing aids, it has the potential to expand teleaudiology initiatives.

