### Trial design {8}

This protocol describes a non-inferiority, double-blind randomised crossover trial to evaluate the effectiveness of using teleaudiology for the programming of hearing aids. Outcomes are measured 4 weeks after each intervention, with a 2-week period between interventions. The study will take 14 weeks for each participant.

This protocol is in accord with the Standard Protocol Items: Recommendations for Interventional Trials (SPIRIT) 2013 statement [22], and the intervention is described according to the Consolidated Standards of Reporting Trials (CONSORT) checklist [23]. See Supplementary material for the complete SPIRIT checklist.

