### Sample size {14}

Sixty participants (thirty per group) will be recruited for the trial. This will provide 90% power at the 5% significance level to detect an overall clinically meaningful difference of 5 dB 4FREAR and allow for up to 10% attrition.

Power analysis was conducted by selecting a random sample of patients from a clinical register and using the variance in REM scores to estimate the expected variance in the research. Power analysis for a 5-dB non-inferiority limit (the acceptable variance in REMs according to the NZAS Best Practice Guidelines) in a continuous outcome in a non-inferiority trial with an alpha level of 5% and 90% power indicates a total sample size of 54 (27 per group). We propose a sample size of 60, which will allow 30 in each hearing loss group and therefore a repeated measures analysis on groups of 30.

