## Statistical methods

### Statistical methods for primary and secondary outcomes {20a}

The difference in REAR measures between interventions will be used as the primary outcome. The data will be modelled as a fully factorialised 5-way mixed-measures ANOVA with repeated measured being: ear (right and left), frequency (500, 1000, 2000, 4000 Hz), REM signal input level (55 dB, 65 dB, 75 dB), and fitting method (in-clinic or remote); and level of hearing loss (mild or moderate) as a between-participant factor.

Secondary analyses of speech intelligibility, hearing-related quality of life, hearing aid benefit, sound quality and preference, and speech-in-noise ability will be conducted in the same way. In the analyses, a main or interaction effect involving fitting method will provide evidence that the in-clinic and remote fitting approaches led to differences in the variables involved. Interactions will be explored using testing of simple effects using follow-up ANOVAs and graphical representations of data including error bars based on the standard error of the mean difference between the points, to represent the repeated measured nature of these variables, and using the standard error of the mean for analysis related to level of hearing loss.

Given the statistical power inherent in the data analysis (repeated measures approach), the sample size should be sufficient. To ascertain the clinical importance of the difference observed at a statistical level, a criterion of + / − 5 dB will be applied to REAR measures, in accordance with best practice guidelines. The secondary outcomes do not have a convention associated with clinical importance, so any statistical effects observed will be discussed in terms of the specific measure and meaningful outcomes in previous research as well as making comparisons based on confidence intervals.

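### The trial is declared non-inferiority with a 5 dB limit, but the stated primary rule tests for no difference and grades the observed difference against ±5 dB, so false acceptance of remote fitting is not controlled

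*Protocol article*

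**What the plan says.** The aim is stated in four places in the Protocol article:

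- Trial design {8}: "This protocol describes a non-inferiority, double-blind randomised crossover trial".
- Sample size {14}: "Power analysis for a 5-dB non-inferiority limit", "in a continuous outcome in a non-inferiority trial with an alpha level of 5% and 90% power", leading to 54 participants and, with attrition, 60. The same section also describes the aim as detecting a 5 dB difference. It states neither the sidedness of alpha nor the SD.
- Abstract, Background: "This study will investigate whether remote hearing aid fittings can provide clinically equivalent outcomes".
- Abstract, Conclusions, where wider use of teleaudiology is made conditional: "If no clinically significant differences are found between in-clinic and remote fit hearing aids".

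The rule for reaching that conclusion is in Statistical methods {20a}. REAR is modelled in a five-way mixed ANOVA with all interactions, and any effect of fitting method, main or interaction, is taken to show that the two approaches differ. Then, "To ascertain the clinical importance of the difference observed at a statistical level", a two-sided 5 dB criterion is applied to REAR. Confidence intervals appear only in the sentence on secondary outcomes. Section {20b} plans no further analysis. Under Outcomes {12}, the primary outcome is an absolute difference in 4FREAR.

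**The concern.** A non-inferiority or equivalence trial must reject the hypothesis that the true difference is as large as the margin. The usual way is to show that a confidence limit, or both limits, falls inside it. The stated rule never does this. The ANOVA tests a difference of zero, and the ±5 dB step looks at the difference that was observed. A finding of no clinically significant difference can therefore be reached while the data remain compatible with a true difference beyond 5 dB.

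The error that matters here is declaring remote fitting acceptable when it is not. The 5% alpha in Sample size {14} is meant to limit that error, but the stated rule does not apply it.

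The direction is also unsettled. Non-inferiority is one-sided, whereas the ±5 dB criterion, the absolute difference in {12} and the guideline tolerance cited in Background and rationale {6a} run both ways. The text fits equivalence better than non-inferiority.

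**Working it through.** **Inputs.** From Sample size {14}: margin 5 dB, alpha 5%, power 90%, 54 before attrition (27 per group). Assumed, because the documents give no SD: SD of the within-person difference from 4 to 12 dB, normal data, 54 complete pairs, and the main effect of fitting method only.

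**1. The plan's own figure.** Attrition reproduces: 54 / (1 − 0.10) = 60. For two parallel groups, n per group = 2 × SD² × (z_α + z_β)² / 5². Solved backwards, 27 per group corresponds to an SD of 6.17 to 6.27 dB if alpha is one-sided 5%, or 5.57 to 5.66 dB if one-sided 2.5%. Without the SD, 54 can be neither confirmed nor refuted.

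**2. The stated rule.** Remote fitting passes if the effect is non-significant or |observed difference| < 5 dB. If the true difference is 5 dB, the estimate falls below 5 dB in half of trials by symmetry, whatever the SD. The non-significance route adds almost nothing: even at SD 12, SE = 12/√54 = 1.633 and the significance threshold is 2.006 × 1.633 = 3.28 dB, already below 5.

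**3. Simulation** (paired t analysis, 54 pairs, 400,000 draws per case), share of trials that accept remote fitting:

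| SD of difference (dB) | True 5 dB: stated rule | True 5 dB: 95% / 90% CI within ±5 | True 6 dB: stated rule | True 6 dB: 90% CI within ±5 |
|---|---|---|---|---|
| 4 | 50% | 2.5% / 5.0% | 3.3% | <0.1% |
| 6 | 50% | 2.5% / 5.0% | 11.0% | 0.2% |
| 8 | 50% | 2.5% / 5.0% | 17.8% | 0.5% |
| 10 | 50% | 2.5% / 5.0% | 23.0% | 0.9% |
| 12 | 50% | 2.5% / 5.0% | 26.9% | 1.2% |

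**4. One concrete result.** Take SD 6 dB and an observed difference of 4 dB. SE = 6/√54 = 0.816 and t = 4/0.816 = 4.9, so the ANOVA-type test is significant. The ±5 dB criterion then grades 4 dB as not clinically important, and remote fitting passes. The 95% CI is 4 ± 2.006 × 0.816, about 2.4 to 5.6 dB, which crosses the margin.

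**5. Which route does the harm.** A non-significant result can have a 95% CI reaching 5 dB only if 2 × 2.006 × SD/√54 > 5, that is, SD above about 9.2 dB. Below that, the damage comes from comparing the point estimate with ±5 dB.

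**6. Power of the corrected test.** With 54 pairs, true difference 0 and 90% power for two-sided equivalence, the largest tolerable SD of the difference is 5√54 / (z_α + 1.645). This gives 36.74/(1.960 + 1.645) = 10.2 dB for a 95% CI and 36.74/(1.645 + 1.645) = 11.2 dB for a 90% CI.

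**The case against.** The strongest defence is that the article is condensed, the analysis plan is not shown, and the ±5 dB criterion could have been meant for an interval. Section {20a} also plans error bars from the standard error of the mean difference. But the article does more than leave detail out. It states a primary analysis and an inference rule, attaches the criterion to the observed difference, and mentions confidence intervals only for secondary outcomes. It would be too much to infer that these data could never support equivalence; what is wrong is the stated rule.

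A reader might also infer that a small but significant effect would count against remote fitting. The text does not support that. A significant 2 dB effect would be reported as a difference and then graded as clinically unimportant, and the abstract's conclusion turns on clinical significance. The fault runs towards accepting remote fitting too easily.

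A third objection stands in part. If 27 per group is a two-group calculation, the implied SD is at most about 6.27 dB. With no negative within-person correlation, the SD of the difference is then at most 6.27 × √2 = 8.9 dB. At that value every non-significant main effect already has its 95% CI inside ±5 dB (largest limit 4.84). Reliance on non-significance alone is then harmless, and examples built on an SD of 12 dB are extreme. The point-estimate route is untouched, and its 50% pass rate at the margin does not depend on the SD.

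Finally, {6a} cites a wider tolerance, ±8 dB, at 4000 Hz, one of the four averaged frequencies. The check uses 5 dB because the plan declares it; it does not judge whether 5 dB suits the average.

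**Conclusion.** The stated primary rule contradicts the declared design and should be corrected before analysis. As written, a true difference at the 5 dB limit is accepted in about 50% of trials, ten times the 5% that a 90% interval rule allows and twenty times the 2.5% of a 95% rule. A true 6 dB difference is accepted in about 3% to 27%, depending on the SD. These figures assume 54 complete pairs, normal data, a single main effect and an SD of the difference between 4 and 12 dB; the 50% does not vary over that range.

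A reader might infer that the sample size is wrong. The documents do not show this, since the SD is unstated.

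**What to change.** 1. In {20a}, make the primary analysis the signed within-participant difference (remote minus in-clinic) in 4FREAR, estimated from the crossover data with its confidence interval. Claim equivalence only if the whole interval lies within −5 to +5 dB.
2. Prespecify one level: 90% if the 5% alpha in {14} is one-sided, 95% if 2.5% on each side is meant.
3. Amend {12}, because an unsigned difference cannot be compared with a lower limit of −5 dB. Bring the non-inferiority wording in {8} and the mix of non-inferiority limit and difference detection in {14} into line.
4. State that a non-significant ANOVA does not support equivalence, and keep the factorial ANOVA as supportive.
5. State the register SD and restate power for this test. At a true difference of 0, 54 completers keep 90% power up to an SD of the difference of about 10.2 dB (95% interval) or 11.2 dB (90% interval).

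The cost is a change of wording and one power calculation, using the same measurements. Whether 60 participants remain enough depends on the SD, so unchanged power should not be promised until it is given.

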### Interim analysis {21b}

There is no planned interim analysis.

### Methods for additional analyses (e.g. subgroup analysis) {20b}

There is no planned additional analysis.

### Methods in analysis to handle protocol non-adherence and any statistical methods to handle missing data {20c}

All treatment evaluations will be performed on the principle of intention-to-treat (ITT), using the observed data collected from all randomised participants. We do not anticipate a large number of participants with missing data due to the nature of the study procedures. Cases will be excluded for analyses where data are missing. Reasons for missing data will be described if known.

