#### First and second interventions

The hearing aids will be programmed with the pre-saved settings that relate to each participant’s group allocation. Two weeks after the final fitting appointment, the participants will be sent the hearing aids via courier. They will be instructed to wear them for at least 8 h per day for 2 weeks.

At the end of these 2 weeks, all participants will have a follow-up appointment via remote support with a clinician who is blinded to the groups. At this appointment, the participants will have the opportunity to have the hearing aid settings adjusted by the clinician in order to optimise the sound for their personal preferences. This process will follow an interview-style approach, with the participant asked to comment on overall volume, overall sound quality, performance in quiet, performance in noise, and perception of own voice. The clinician will make small adjustments to the hearing aid settings until the participant is satisfied with the sound.

Participants will be instructed to wear the hearing aids for a further 2 weeks, and then return to the clinic for the first outcome assessment. The hearing aids will be returned to the clinic at this time.

The second intervention will follow the same process as the first, with the hearing aids programmed with the alternate settings.

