### Strategies to improve adherence to interventions {11c}

Adherence can be monitored at 2-week intervals through hearing aid data-logging software that includes use-tracking data.

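### A declared non-inferiority trial fixes intention-to-treat as its only analysis set and gives logged wear time no role, leaving dilution of the self-report contrasts unchecked

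*Protocol article*

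**What the plan says.** Under Trial design {8} the study is a "non-inferiority, double-blind randomised crossover trial". Under First and second interventions, participants get the aids by courier and a wear instruction: "They will be instructed to wear them for at least 8 h per day for 2 weeks". A remote adjustment session follows, then two more weeks of wear for which no daily hours are given.

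Under Strategies to improve adherence {11c}: "Adherence can be monitored at 2-week intervals through hearing aid data-logging software that includes use-tracking data". The verb is permissive, and neither Statistical methods {20a} nor the non-adherence section {20c} mentions wear time.

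Section {20c} sets the analysis population: "All treatment evaluations will be performed on the principle of intention-to-treat (ITT), using the observed data collected from all randomised participants". It adds: "Cases will be excluded for analyses where data are missing". The section on additional analyses {20b} reads in full: "There is no planned additional analysis".

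**The concern.** When the aim is to show that one fitting is not worse than another, anything that makes the two look alike favours the claim. Intention-to-treat is then not automatically the cautious choice, and it is usual to set a supportive analysis in adherent participants beside it. Here the protocol makes intention-to-treat the population for every evaluation and plans nothing further. That is a stated commitment, not a detail left open for a statistical analysis plan: a later plan that added an adherent set would contradict {20b} and {20c}.

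The route to dilution is concrete. Participants have at least one year of hearing aid experience (Eligibility criteria {10}), and the study aids take the place of aids they already own ({11d}). Someone who goes back to their own aids in both periods answers the HHIA, APHAB and sound-quality items with little experience of either fitting. Participants stay in the study unless they withdraw ({11b}), so such a person stays in every comparison for which data exist.

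At stake is how a null result on the self-report outcomes is read. Statistical methods {20a} takes an effect of fitting method as the evidence of a difference, and the Abstract's conclusions say that finding no clinically significant differences could expand teleaudiology. A diluted contrast would be read as support for that.

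**Working it through.** **1. The plan's own figures.** Sample size {14} gives a 5 dB limit, alpha 5%, 90% power, and 54 participants (27 per group), raised to 60 for 10% attrition. The attrition step reproduces: 54 / 0.9 = 60. The 27 per group cannot be strictly reproduced, because neither the SD nor the sidedness of alpha is stated. With the two-group formula n = 2(z₁₋α + z₀.₉₀)² SD² / 5²:
- one-sided 0.05, SD 6.2 dB: 2 × (1.645 + 1.282)² × 38.44 / 25 = 26.3, rounded up to 27;
- one-sided 0.025, SD 5.6 dB: 2 × (1.960 + 1.282)² × 31.36 / 25 = 26.4, rounded up to 27.

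These SDs are back-solved assumptions.

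**2. Which outcomes non-wear can dilute.**
- *HHIA, APHAB, sound quality and preference:* they rest on experience with each fitting, so dilution toward no difference is credible.
- *4FREAR:* a clinician measures it in clinic with the aid in the ear (Primary outcome). It starts from settings saved before randomisation and then passes through one adjustment session per period (First and second interventions). A non-wearer still yields the output of each programmed fitting. Wear acts only through feedback at that session. Little feedback tends to leave the original difference in place, while adjustment toward personal preference could make the fittings converge. The direction is not established.
- *SII and aided QSIN:* the first is calculated from the REAR and the second is tested in clinic, so both are less exposed.

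**3. Size of the dilution, self-report outcomes.** Suppose a share p of participants contributes no contrast and the rest have true difference d. The expected difference is (1 − p)d: 0.9d, 0.8d and 0.7d for p = 0.1, 0.2 and 0.3. The documents give no wear rate, so p is an assumption.

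**4. Cost in precision of an adherent set.** Let p now be the non-adherent share per period, with periods independent (assumption). Requiring adherence in both periods keeps (1 − p)² of participants, and the confidence interval widens by 1/√((1 − p)²) = 1/(1 − p).

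| p per period | kept | CI widening |
|---|---|---|
| 0.1 | 81% | 11% |
| 0.2 | 64% | 25% |
| 0.3 | 49% | 43% |

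If the same people fail in both periods, 1 − p are kept and the widening is 1/√(1 − p): 5%, 12% and 20%.

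**5. Power of the adherent set on 4FREAR.** With true difference 0 and the parallel-group SDs of step 1, power = Φ(5 / (SD √(2/n)) − z₁₋α), where n = 27(1 − p)². At one-sided 0.05 and SD 6.2 this gives 0.85, 0.77 and 0.67 for p = 0.1, 0.2 and 0.3. At one-sided 0.025 and SD 5.6 it gives 0.84, 0.75 and 0.63. With n = 27(1 − p), where the same people fail in both periods, the figures are 0.88, 0.84 and 0.80, and 0.88, 0.84 and 0.78. The set can support a consistency check, but at the higher rates it is too small to serve as a second gate.

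**The case against.** The strongest reply is that the usual warning about intention-to-treat does not fit this primary outcome. 4FREAR measures device output, the clinic loads the settings, and participants do not choose the file, so there is little room for treatment contamination. If less wear means less adjustment, non-wear may preserve a difference and make intention-to-treat the more cautious analysis. This stands. A reader might infer that non-wear makes the two fittings look alike on the primary outcome and so threatens the non-inferiority claim directly; the documents do not support that reading.

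Second, the 5 dB limit applies to REAR only, and {20a} says the secondary outcomes have no convention of clinical importance. A rule that both analyses must clear a margin therefore cannot be applied where dilution is most credible. This stands too. Nor should the two analyses be required to agree in direction: with a true difference near zero, the estimates can differ in sign by chance while both intervals lie well inside 5 dB.

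Third, wear is a response to the fitting. Someone who dislikes one fitting may wear it less, and a filter on wear in both periods removes that person, which can itself bias toward similarity. This stands, and it is why the adherent set can be supportive only.

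Fourth, experienced users may wear the aids well, and the documents give no wear rate to suggest otherwise. That limits the likely size of the problem. It does not explain why available wear data should go unused, nor does an unknown direction for 4FREAR justify planning no check.

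**Conclusion.** The point holds as a cheap improvement. The protocol commits a declared non-inferiority trial to a single analysis set, plans no additional analysis, and leaves loggable wear time optional and unused. The exposure lies mainly in HHIA, APHAB, and sound quality and preference, where a share of 10% to 30% of participants without contrast would shrink a true difference by 10% to 30%. Those shares are illustrative, and the calculation assumes that non-wearers contribute exactly zero contrast.

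For 4FREAR no bias in either direction has been shown. The case there is only that the outcome is measured after an adjustment informed by wear, so a consistency check is worth having.

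The wear instruction should not be over-read as a ready-made adherence threshold: the daily hours are attached to the first two weeks of a period, and the second two weeks carry none. Separately, excluding cases with missing data makes the analysis complete-case in practice, which sits uneasily with an intention-to-treat label covering all randomised participants.

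**What to change.** - **Adherence section {11c}:** state that wear time will be downloaded at each 2-week point, in place of saying that it can be monitored.
- **Non-adherence section {20c}:** keep intention-to-treat as the primary analysis. Pre-specify, before unblinding, one supportive analysis: either participants whose logged mean wear meets the protocol's own wear instruction in both periods, stating which weeks count, or a model with wear time as a continuous variable.
- **Use of the results:** for the self-report outcomes, use it to interpret the intention-to-treat result. For 4FREAR, report whether the adherent-set confidence interval also lies within the 5 dB limit and discuss any discrepancy, with no requirement that the two analyses agree in direction.
- **Descriptive reporting:** give wear time by fitting method, so that a reader can see whether one fitting was worn less.
- **Additional analyses {20b}:** align the text with the above.

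The cost is one further analysis of data the aids can already log. The adherent set is self-selected on a post-randomisation response and may itself be biased, and its intervals will be wider, as shown in the working. The report should state both limits.

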### Implementation {16c}

All participants who meet the eligibility criteria and complete the in-clinic and remote hearing aid fitting process will be randomised and assigned to an intervention group by a trained clinical research assistant. The research assistant will generate the allocation sequence.

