## Assignment of interventions: blinding

### Who will be blinded {17a}

This is a double-blind study. Both the participants and the clinicians will be blind to the allocation of groups and order of intervention. The hearing aid settings and real-ear measurements will be stored anonymously so that the clinician is unable to determine what fitting process was used. The participants and clinicians will be aware of the intervention strategy at the fitting process (in-clinic or remote), which occurs prior to group allocation and blinding.

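### The stated missing-data rule turns an analysis labelled intention-to-treat into a complete-case one, and fitting failures before randomisation should be reported beside the result

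*Protocol article*

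**What the plan says.** The section on non-adherence and missing data {20c} sets the principle: "All treatment evaluations will be performed on the principle of intention-to-treat (ITT), using the observed data collected from all randomised participants". It expects few gaps ("We do not anticipate a large number of participants with missing data due to the nature of the study procedures"), and then fixes the rule: "Cases will be excluded for analyses where data are missing". It also undertakes to describe reasons for missing data where known.

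The statistical methods section {20a} specifies a fully factorial five-way mixed ANOVA. The repeated factors are ear (2), frequency (4), input level (3) and fitting method (2), and hearing-loss level is the between-participant factor. Secondary outcomes are to be analysed in the same way. No additional analyses are planned {20b}.

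The sample size section {14} requires 54 participants and recruits 60, to "allow for up to 10% attrition".

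On entry to the randomised set, Implementation {16c} states: "All participants who meet the eligibility criteria and complete the in-clinic and remote hearing aid fitting process will be randomised". The blinding section {17a} confirms that the fitting is a step "which occurs prior to group allocation and blinding".

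**The concern.** Two sentences in the same paragraph do not fit together. A randomised participant with partial data has observed data, and the second sentence discards them from any analysis in which something is missing. How much is lost depends on the model. A conventional repeated-measures ANOVA needs a full set of cells for each participant, so one unusable recording, one ear or one missed visit removes that participant's remaining real-ear data from the primary analysis. A reader who sees the intention-to-treat label would not expect this.

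A second, separate matter is what the conclusion covers. Remote fitting depends on an app, Bluetooth pairing and a live connection. Someone for whom this cannot be completed is never randomised, and the article does not say that such people are counted. Trial design {8} states the aim as evaluating the effectiveness of teleaudiology for programming hearing aids, which is wider than a comparison among people in whom both fittings succeeded.

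**Working it through.** **Inputs.** Required N 54, recruited 60, attrition 10%, margin 5 dB, power 90%, alpha 5% with sidedness not stated (Sample size {14}). Two ears, four frequencies, three input levels, two fitting methods (Statistical methods {20a}). One outcome visit per method, in weeks 8 and 14 (Outcomes {12}). Missingness rates are not given, so those below are assumptions.

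**1. The plan's own figure.** 54 / (1 − 0.10) = 60. It reproduces exactly, so the allowance has no slack: any loss above 10% takes the trial below its own required N.

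**2. Units that can go missing.** The ANOVA has 2 × 4 × 3 × 2 = 48 cells per participant. The four frequencies are read from one recorded response per ear and level, so the separate recordings number 2 ears × 3 levels × 2 visits = 12.

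**3. Participants removed if one missing unit removes the participant.** Loss = 1 − (1 − p)^k, for k units missing independently with probability p.

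| Assumption | Formula | Participants lost | Left of 60 | Left of 54 (10% attrition already spent) |
|---|---|---|---|---|
| 0.5% per recording | 1 − 0.995^12 | 5.8% | 56.5 | 50.8 |
| 1% per recording | 1 − 0.99^12 | 11.4% | 53.2 | 47.9 |
| 2% per ear-visit (2 ears × 2 visits) | 1 − 0.98^4 | 7.8% | 55.3 | 49.8 |

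**4. Effect on power.** No SD is given. If 54 is read as the number of paired participants, the SD of the difference implied by the stated N is 5 × √54 / (z for alpha + z for 90% power). This gives 12.56 dB at one-sided 5% and 11.33 dB at one-sided 2.5%. With power = Φ(5 × √N / SD − z for alpha), the result is 90% at 54, about 88% at 51 and 86–87% at 48. The loss of power is modest.

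**5. A case that needs no assumed rate.** A participant measured at week 8 who withdraws before week 14 has 2 × 4 × 3 = 24 observed cells. Under the stated rule with a conventional ANOVA, none of them is used. A mixed model would keep them, but with only one fitting method observed they add little to the within-person contrast between methods. The mixed model gains most when an ear or a level is missing and the rest of both visits is intact.

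**6. Fitting before randomisation.** Implementation {16c} defines the randomised set as those who completed both fittings. Failures of the remote fitting therefore fall outside the phrase "using the observed data collected from all randomised participants" by construction. No rate of failure can be derived from the article.

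**The case against.** The paragraph can be read as an available-case analysis without imputation: everyone randomised is eligible for each analysis, and exclusion operates analysis by analysis. That is right as far as it goes. A reader might infer that any incomplete participant is deleted from the whole trial, and the text does not say so. It does not save the intention-to-treat label for the primary analysis, because there the whole participant would conventionally drop out.

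A reader might also treat the 48 cells as independently missing, which at 0.5% and 1% per cell gives losses of 21% and 38%. The document does not support this, since four frequencies come from one recording. Clustering by ear or visit lowers the figures further, and an in-person clinician may be able to repeat a failed recording.

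Power may be safer than step 4 suggests. If 27 per group came from a parallel-group formula, the implied SD at one-sided 5% is 6.28 dB. A paired comparison with non-negative within-person correlation then needs at most (1.645 + 1.282)² × 2 × 6.28² / 5² ≈ 27 participants in total. This stands, and it is why the point rests on the analysis set and its label more than on power.

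The tempting stronger reading is that randomising after both fittings itself breaches intention-to-treat. It does not. That principle starts at randomisation, randomisation here sets only the order in which two stored settings are worn, and the within-person difference does not exist without both fittings. The design also limits failures: internet access is required, phones are lent, app installation is guided in clinic and pairing is confirmed by telephone.

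Finally, missing-data detail often sits in an analysis plan that is not shown. Here, however, the protocol states a rule, and that rule conflicts with the principle beside it.

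**Conclusion.** The point holds in a limited form. The stated rule, combined with the stated ANOVA, gives a complete-case primary analysis under an intention-to-treat label. On the assumed rates above, about 6% to 11% of participants would be removed, against an allowance of 10% that exactly covers the step from 60 to 54. These figures rest on assumed rates, on independence between recordings or ear-visits, and on conventional listwise handling in the ANOVA. The article itself expects little missing data, so the actual loss could be smaller.

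The timing of randomisation is a matter of scope, not an error of analysis. The result will describe people in whom remote fitting could be completed. The size and direction of any difference from remote fitting as a service cannot be worked out from the document.

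**What to change.** - Analyse REAR with a linear mixed model using every observed measurement from all randomised participants. Fixed effects: fitting method, period, sequence, hearing-loss level, ear, frequency and input level. Include a random participant effect, and a covariance structure that recognises readings sharing a visit, so that they are not counted as independent evidence.
- Keep the complete-case ANOVA as a sensitivity analysis. If the ANOVA stays primary, call the set complete-case and drop the intention-to-treat label.
- Report, among all consented participants, the number not completing each fitting (in-clinic and remote) with reasons, beside the primary result. Limit the conclusion to people in whom remote fitting could be completed.

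The cost is slightly more modelling work and a simple count. The article does not say that fitting failures are logged, so the count should be set up before recruitment. Under section {25}, protocol changes go to the ethics committee. Randomisation, visits and measurements do not change.
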